# The Pocket-4-Life project, bioavailability and beneficial properties of the bioactive compounds of espresso coffee and cocoa-based confectionery containing coffee: study protocol for a randomized cross-over trial

**DOI:** 10.1186/s13063-017-2271-2

**Published:** 2017-11-09

**Keywords:** Coffee, Cocoa, Bioavailability, Pharmacokinetic, Cardiometabolic risk factors, Caffeoylquinic acid, Flavan-3-ols, Caffeine, Trigonelline, Diterpenes

## Abstract

**Background:**

Coffee is an important source of bioactive compounds, including caffeine, phenolic compounds (mainly chlorogenic acids), trigonelline, and diterpenes. Several studies have highlighted the preventive effects of coffee consumption on major cardiometabolic diseases, but the impact of coffee dosage on markers of cardiometabolic risk is not well understood. Moreover, the pool of coffee-derived circulating metabolites and the contribution of each metabolite to disease prevention still need to be evaluated in real-life settings. The aim of this study will be to define the bioavailability and beneficial properties of coffee bioactive compounds on the basis of different levels of consumption, by using an innovative experimental design. The contribution of cocoa-based products containing coffee to the pool of circulating metabolites and their putative bioactivity will also be investigated.

**Methods:**

A three-arm, crossover, randomized trial will be conducted. Twenty-one volunteers will be randomly assigned to consume three treatments in a random order for 1 month: 1 cup of espresso coffee/day, 3 cups of espresso coffee/day, and 1 cup of espresso coffee plus 2 cocoa-based products containing coffee twice per day. The last day of each treatment, blood and urine samples will be collected at specific time points, up to 24 hours following the consumption of the first product. At the end of each treatment the same protocol will be repeated, switching the allocation group. Besides the bioavailability of the coffee/cocoa bioactive compounds, the effect of the coffee/cocoa consumption on several cardiometabolic risk factors (anthropometric measures, blood pressure, inflammatory markers, trimethylamine N-oxide, nitric oxide, blood lipids, fasting indices of glucose/insulin metabolism, DNA damage, eicosanoids, and nutri-metabolomics) will be investigated.

**Discussion:**

Results will provide information on the bioavailability of the main groups of phytochemicals in coffee and on their modulation by the level of consumption. Findings will also show the circulating metabolites and their bioactivity when coffee consumption is substituted with the intake of cocoa-based products containing coffee. Finally, the effect of different levels of 1-month coffee consumption on cardiometabolic risk factors will be elucidated, likely providing additional insights on the role of coffee in the protection against chronic diseases.

**Trial registration:**

ClinicalTrials.gov, NCT03166540. Registered on May 21, 2017.

**Electronic supplementary material:**

The online version of this article (doi:10.1186/s13063-017-2271-2) contains supplementary material, which is available to authorized users.

## Background

Coffee is one of the most popular beverages worldwide and, indeed, its consumption is a moment of pleasure in the daily life of many millions of people. Coffee ranks as the main source of four recognized bioactive constituents within the Mediterranean diet: the purine alkaloid caffeine (1,3,7-trimethylxanthine), the pyridine alkaloid trigonelline, (poly)phenolic substances (mainly chlorogenic acids), and the pentacyclic diterpenes cafestol and kahweol [1]. This unique combination of phytochemicals, with proven biological properties, turns coffee into a dietary agent able to impact on human health [2].

The beneficial properties associated to regular coffee consumption have been clearly described by an important number of systematic reviews and meta-analyses [3–9]. The beverage is associated with a reduced risk of several chronic pathologies related to inflammation processes, such as atherosclerotic heart disease, stroke, and type 2 diabetes, as well as neurodegenerative conditions [4–6, 10–13]. Most of these observations have also emphasized the dose-response inverse relationship of long-term coffee consumption with disease risk. Similarly, the non-linear U-shaped curve linking coffee consumption and cardiovascular disease (CVD) might be due to a combination of beneficial and detrimental effects [4, 14]. However, although observational studies provide the first line of evidence on a causal relation between coffee intake and risk of cardiometabolic diseases, randomized trials are required to address this point definitively [6, 15, 16]. This need for intervention studies has received little attention and, despite some progresses being made [17–19], most of research to date has failed to elucidate the rationale behind the potential preventive effects of coffee consumption. Arguably this can be attributed to the lack of an association of the physiological responses with the coffee bioactives in the circulation. In this sense, coffee is a complex mixture, with dozens of chemicals appearing in the circulatory system after consumption, absorption and metabolism, and where individual circulating metabolites may exert different effects within the human body [20, 21]. The complete pool of coffee-derived circulating metabolites and the contribution of each metabolite to disease prevention are still unknown.

The co-presence in the circulation of different plant-derived metabolites with proven biological activities is a key factor on the prevention of cardiometabolic diseases through adequate dietary habits [1, 22–24]. Among the vegetal matrixes with high content in bioactive phytochemicals, cocoa is gaining increasing attraction. Many initiatives such as the EU FP7 project FLAVIOLA and the COSMOS trial have been carried out in order to assess the efficacy of flavan-3-ols, the main flavonoids in cocoa/chocolate, towards surrogate markers of cardiovascular function, with some of these obtaining positive health claims [25–29]. Cocoa and chocolate also contain high amounts of theobromine (3,7-dimethylxanthine) a closely related analog of caffeine [30]. Cocoa-based products are, therefore, an interesting target that could synergize the preventive cardiometabolic effects of regular coffee consumption. In this sense, chocolate confectionary containing coffee, combining the phytochemical content of coffee and cocoa, could be regarded as a potential candidate to enhance the circulating levels of putatively protective metabolites in the context of a balanced diet.

This work will help to define the bioavailability and beneficial properties of coffee bioactive compounds on the basis of different levels of coffee consumption. Moreover, the contribution of cocoa-based products containing coffee to the pool of circulating metabolites and their putative bioactivity will be taken into account. This innovative study design guarantees adherence to real life settings and patterns of consumption, which will serve to unravel critical gaps within the framework of nutritional intervention studies with coffee.

## Methods/Design

### Objectives

With ultimate aim of studying the bioavailability of coffee/cocoa bioactive compounds and their effects in cardiometabolic health, the objectives of this intervention will be:(i)ssessing the bioavailability of the four main groups of phytochemicals in roasted coffee (methylxanthines, phenolic compounds, trigonelline, and diterpenes), its modulation by the level of consumption, and establishing the daily average concentration of coffee-derived plasma circulating metabolites;(ii)investigating the effect of different levels of coffee consumption on cardiometabolic risk factors;(iii)evaluating circulating metabolites and their putative bioactivity when substituting coffee consumption with the intake of cocoa-based products containing coffee.

### Protocol and study design

A human study will be carried out to achieve the above-described goals. The human intervention study will consist of a short-term, randomized cross-over trial, addressed at measuring the daily mean concentrations of each coffee/cocoa-derived circulating metabolite (CCDCM) for the four main groups of coffee/cocoa phytochemicals (methylxanthines, trigonelline, phenolics, diterpenes). On the basis of different patterns of consumption, this free-living study (although some minimal dietary restrictions will be introduced two days before sampling times) will also take into consideration the effects of repeated doses on the bioavailability of coffee/cocoa bioactives.

The study will follow a repeat-dose, 3-arm, cross-over design as shown in Figs. 1 and 2 (SPIRIT chart). This design has been chosen according to ILSI’s guidelines for intervention trials with dietary products [31]. The protocol was also developed in accordance with the Standard Protocol Items: Recommendations for Interventional Trials (SPIRIT) Statement (SPIRIT checklist presented as Additional file 1).

**Fig. 1 Fig1:**
[figure not shown]
Study design and sampling day (in the blue box) scheme. *HC* high consumers, *LC* low consumers, *MC* medium consumers, *SD* sampling day

**Fig. 2 Fig2:**
[figure not shown]
SPIRIT figure: summarizes the allocation, interventions, and outcomes of the study

Subjects will be assigned to consume the following treatments in a random order for one month (including the sampling day -the last day of each intervention period-):one cup of espresso coffee/day (“low consumers”) at 9.00 AM;three cups of espresso coffee/day (“high consumers”) at 9.00 AM, 12.00 PM, and 3.00 PM;one cup of espresso coffee at 9.00 AM and two cocoa-based products containing coffee two times per day, at 12.00 PM and 3.00 PM. This group will be named “medium consumers”, in view of the caffeine content of the cocoa-based product containing coffee.

Minimal recommendations to avoid other sources of coffee/cocoa-related phytochemicals besides those introduced through the assigned treatment, and to standardize the time of coffee consumption, will be provided for the 2 days prior to each sampling day and on the sampling day. Dinner timing and composition will also be standardized the day before the sampling day. Only water could be drunk during the night. In the morning of the sampling day, the subjects will attend a clinic where fasting baseline blood and urine samples will be collected. Then, low and high consumers will drink one or three cups of espresso coffee, respectively (without sugar, sweeteners, and milk for the first coffee; with 5 g of sugar for the last two coffees), while medium consumers will drink a cup of espresso coffee and two cocoa-based products containing coffee twice during the course of the day, following the above mentioned timing. After ingestion of the first coffee together with a polyphenol-free breakfast (a sponge milky cake), blood and urine samples will be collected at selected time points over the ensuing 24-h time points (Fig. 1). Five hours after the consumption of the first coffee, participants will receive a standardized mixed meal (ham and cheese sandwich) free of coffee/cocoa-related phytochemicals. Water will be available ad libitum. Twenty-four hours after receiving the treatment, blood and urine samples will also be taken in order to assess return to baseline. In addition, anthropometric characteristics and blood pressure will be measured.

### Testing materials and phytochemical composition

Volunteers will be supplied with a single-serve coffee machine (Essenza EN 97.W, De’Longhi Appliances S.r.l, Treviso, Italy) and coffee capsules (Capriccio, Nespresso Italia S.p.a., Assago, Italy) to standardize brewing method, raw material, and cup volume (approximately 45 mL). Volunteers will also be supplied with the cocoa-based product containing coffee (Pocket Coffee, Ferrero Commerciale Italia S.r.l., Alba, Italy). The content in phytochemicals of the coffee and the cocoa-based product containing coffee will be analyzed by ultra-performance liquid chromatography-tandem mass spectrometry (UHPLC-MS/MS) following methodologies described in previous reports [32–35]. Accurate calibration and absolute quantification will be achieved by comparison with authentic standards. The amount of caffeine provided by a cup of espresso coffee is approximately 60 mg/serving, while two cocoa-based products containing coffee provide approximately 30 mg of caffeine.

### Participant selection

Twenty-one healthy volunteers will be recruited in Parma (North Italy) for the study, using announcements placed in university, hospital, and public places. All subjects potentially involved in the nutritional intervention will be informed of the details of the protocol and about the risks associated with participation. Those who agree to participate will be asked by the study staff for their written informed consent to participate in the study. Information to the volunteers will be provided before and separately from the consent form. Personal data collection will include names, e-mail, phone number, age, height, weight, and dietary habits of the volunteers.

### Inclusion and exclusion criteria

Inclusion criteria will include being adult, healthy, of normal weight [body mass index (BMI) 18–25], and regular consumers of one to five cups of coffee per day. Exclusion criteria will include clinical diagnosis for metabolic, renal or digestive disorders, regular consumption of medication, antibiotic therapy taken within the last 3 months, intense physical activity, pregnancy or lactation, regular intake of coffee exceeding five coffees per day, and very high consumption of coffee/cocoa-related phytochemicals. These criteria are set in order to avoid likely confounding factors [36].

### Data and sample collection

Socio-demographic variables will be assessed through a generic questionnaire completed at recruitment. The questionnaire will also contain questions useful to identify possible exclusion criteria (e.g. diagnosis for diseases, regular consumption of medication, food allergy). Dietary habits of volunteers will also be evaluated during the enrollment, through a semi-quantitative food frequency questionnaire (FFQ) for the assessment of dietary total antioxidant capacity [37]. In addition, volunteer’s food intake and compliance with the study requirements will be assessed by means of 3-day dietary records, administered throughout each intervention period at two time points: (i) in the middle of each intervention period during 2 weekdays and a weekend day, and (ii) at the end of each intervention period, 2 days prior to the sampling day and the sampling day. The habitual physical activity level of each participant will be measured through a validated International Physical Activity Questionnaires [38].

Blood sample collection will be carried out in the clinic unit of the Department of Medicine and Surgery. Blood collection will be carried out by a physician. A venous catheter will be inserted into the antecubital vein and blood samples from each subject will be collected in specific tubes at the time points indicated at Fig. 1. Blood at 24 h after first coffee consumption will be taken by venipuncture. Urine samples will be collected during different periods of time (Fig. 1) using urine collectors.

Blood samples will be centrifuged and plasma, serum, and peripheral blood mononuclear cells (PBMCs) will be collected, aliquoted, and stored at -80 °C for further processing. The volume of urine excreted will be measured and aliquots stored at -80 °C for further processing.

### Measurements

The primary selected endpoint of the study is the quantification of the daily mean concentration of coffee-derived plasma circulating phenolic metabolites, whereas the study of the bioavailability of other coffee-derived circulating bioactives, the bioavailability of cocoa-derived circulating phytochemicals, and the assessment of cardiometabolic markers will be considered secondary endpoints.

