### Pharmacokinetic studies

Metabolite data will be analyzed using the WinNonlin software (Certara, LP, Princeton, NJ, USA). Pharmacokinetic parameters of each volunteer will include maximum, minimum, and average plasma concentration (C_max_, C_min_, and C_avg_), degree of fluctuation, area under the curve from 0–24 hours (AUC_0–24_), times of maximum and minimum plasma concentrations (T_max_ and T_min_), and they will be calculated for each metabolite (Fig. 3). Urinary excretion kinetics will also be estimated.

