### Sample size calculation, randomization and statistical analysis

The sample size has been calculated considering the primary outcome, the daily mean concentration of coffee-derived plasma circulating phenolic metabolites, and according to Lenth [55]. Considering the lack of literature dealing with this outcome, the AUC of dihydrocaffeic acid-3′-sulfate, one of the most representative coffee-derived phenolic metabolites [56], has been used for sample size calculations. Keeping a 80% power and an α of 5%, and considering data from Stalmach et al. [56], 15 subjects will have to complete an acute intervention to detect a change of 600 nmol/h/L^-1^ in dihydrocaffeic acid-3′-sulfate plasma concentration with a standard deviation of 870 nmol/h/L^-1^. A total of 21 subjects will be recruited to allow for dropouts and for nonparametric statistical analysis (15% additional subjects required). Power calculation will be retrospectively calculated for the secondary cardiometabolic outcomes (post hoc sample size calculation). Once the volunteers have been recruited, a randomization list will be generated using a randomized block design by means of Random Number Generator Pro (Segobit Software). This list will be made by a colleague not involved in subject enrollment, and using a numbered sequence in sealed, opaque envelopes. It will be blind for the Principal Investigator (PI) and volunteers.

Before any comparison is performed, the normality of each variable will be evaluated to choose the most appropriate statistical test. If normally distributed, data will be expressed as mean ± standard deviation and analyzed using general linear models for repeated measures with post hoc comparisons. If data are not normally distributed, they will be reported as median and interquartile range and the Friedman test with post hoc pairwise comparisons will be performed. Multivariate analyses will be carried out to understand individual responses to coffee consumption on the basis of metabolite production. All the analyses will be carried out using SPSS 23.0 (IBM Corp., Armonk, NY, USA). *P* value <0.05 will be regarded as statistically significant.

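### The primary endpoint is an unlisted set of phenolic metabolites with no lead variable or contrast fixed, while the power statement covers one metabolite and one change

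*Protocol article*

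**What the plan says.** - **Endpoint.** Measurements defines the primary endpoint as the "quantification of the daily mean concentration of coffee-derived plasma circulating phenolic metabolites". Other coffee bioactives, cocoa-derived compounds and the cardiometabolic markers are secondary.
- **Level of analysis.** Protocol and study design describes the trial as "measuring the daily mean concentrations of each coffee/cocoa-derived circulating metabolite (CCDCM"). Pharmacokinetic studies lists the average concentration, AUC from 0 to 24 hours, maximum, minimum and other parameters, and says "they will be calculated for each metabolite".
- **Test.** The statistics section checks normality variable by variable. It then uses a repeated-measures general linear model or a Friedman test over the three treatments, each followed by post hoc comparisons. The threshold is general: a P "value <0.05 will be regarded as statistically significant". No contrast among one cup, three cups and one cup plus cocoa product is named as primary.
- **Sizing.** Because literature on the outcome is lacking, the AUC of dihydrocaffeic acid-3'-sulfate is used, described as "one of the most representative coffee-derived phenolic metabolites". The settings are "Keeping a 80% power and an α of 5"%, and "15 subjects will have to complete an acute intervention to detect a change of 600 nmol/h/L" "with a standard deviation of 870 nmol/h/L". Twenty-one are to be recruited. The sizing metabolite is not declared to be the primary variable.

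**The concern.** A primary endpoint should lead to one identifiable test, or to a defined set of tests with a stated rule for combining them. Here the set has no listed members and no stated size, and three arms leave three possible pairwise contrasts. A reader of the results could not tell from the plan which comparison was meant to carry the primary conclusion. If several metabolites are each compared at 5%, the chance of a false positive somewhere in the primary family exceeds 5% by an amount that the plan neither bounds nor allows for. The planned power has the same gap: it was worked out for one variable and one change, and says nothing about detecting differences across the family.

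**Working it through.** **1. Reproducing the plan's figure.** Inputs from the statistics section: change 600, standard deviation 870, α 5%, power 80%. The article does not state sidedness or which standard deviation 870 is. Take a paired comparison with 870 as the standard deviation of the difference:

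d = 600/870 = 0.690.

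- Paired t (noncentral t), one-sided 5%: n = 15, power 81.4%. This matches the stated 15.
- Normal approximation, two-sided 5%: (1.960 + 0.842)² / 0.690² = 16.5, so 17.
- Paired t, two-sided 5%: n = 19.

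Inflation: 15 × 1.15 = 17.25, so 18, which leaves 3 of the 21 for dropouts. The recruitment figure is consistent. Each of these calculations concerns one metabolite and one contrast.

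**2. Two-sided power for that single test (paired t, α 5%).**

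| Completers | Power |
|---|---|
| 15 | 70.0% |
| 18 | 78.7% |
| 19 | 81.1% |
| 21 | 85.2% |

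If 870 were instead a per-period standard deviation with within-person correlation ρ, the standard deviation of the difference would be 870 × √(2(1 − ρ)). The two-sided requirement would then be 26 at ρ = 0.3, 19 at ρ = 0.5, 16 at ρ = 0.6 and 12 at ρ = 0.7.

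**3. False-positive chance across metabolites.** The number of primary metabolites k is not in the document, so a range is assumed. With one test per metabolite at 5% and no true differences, the independent case is 1 − 0.95^k. The correlated cases come from simulating equicorrelated normal test statistics.

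| k | Independent | Correlation 0.5 | Correlation 0.8 |
|---|---|---|---|
| 5 | 22.6% | 18% | 13% |
| 10 | 40.1% | 29% | 17% |
| 20 | 64.2% | 42% | 22% |

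**4. Across the three arms, one metabolite.** In a simulation with 15 completers, normal data and no true differences, three unadjusted pairwise t-tests give at least one P<0.05 in about 12% of trials. If pairwise tests are read only after a significant overall test, the figure is about 5%.

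**5. Cost of covering the whole family instead.** Bonferroni at 0.05/k, paired t, two-sided, d = 0.690 for every metabolite:

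| k | Completers for 80% power | Power at 15 | Power at 21 |
|---|---|---|---|
| 5 | 28 | 41% | 63% |
| 10 | 32 | 31% | 52% |
| 20 | 36 | 22% | 41% |

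The planned 21 would not support a Bonferroni-controlled family of this size at 80% power. They do support a single two-sided test if at least 19 complete.

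**The case against.** **The endpoint is descriptive.** It is worded as a quantification, and part of the first objective is to establish average concentrations, so much of the trial is estimation. That is fair, and no success criterion is written. A reader might infer that any metabolite or arm pair below 0.05 would count as a positive trial; the article gives only a per-test convention and does not say that. The same objective also covers how bioavailability changes with level of consumption, and the outcome was sized with power and α, so a comparison is intended.

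**The singular word concentration could mean a total.** No total is defined, and the design and pharmacokinetic sections both work per metabolite. That each metabolite is tested at 0.05 is nonetheless an inference from three sections read together.

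**The power calculation is relevant.** A reader might infer that it applies to no primary test. That goes too far. The sizing metabolite belongs to the primary family, and over a fixed 0 to 24 hour window the average concentration is AUC divided by 24, so the ratio of change to standard deviation is unchanged. The valid criticism is that it covers one member only.

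**The overall test protects the arm comparisons.** Largely so within a metabolite, if post hoc tests follow a significant overall test. The post hoc method is unnamed, which does not make it uncorrected. Nothing in this protects across metabolites.

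**The error rates are upper-end.** Metabolites from the same dose and plasma samples are likely to be correlated, and no difference at all is implausible when arms differ threefold in cups. The correlated columns are the answer to the first part; the second limits how literally any of these rates should be taken.

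**An analysis plan not shown may hold a correction.** It may. Which variable and contrast are primary is still a matter for the protocol, and a correction needs a defined family.

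**Conclusion.** The point holds in this form: the primary variable is an unlisted family, no lead metabolite, total or contrast is fixed, and the 80% power refers to one metabolite and one change. The inflation is about 23% to 64% under independence and 13% to 22% at correlation 0.8. It rests on an assumed 5 to 20 metabolites, one test each at 5% and no true differences. The power figures rest on 870 being the standard deviation of the paired difference; on that reading the stated 15 is reproduced only by a one-sided test.

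A reader might extend the point to the roughly 40 cardiometabolic outcomes that can be counted in the measurement sections. The article does not support that as an error: these outcomes are labelled secondary, their power is left to retrospective calculation, and correction for secondary outcomes is commonly left to an analysis plan.

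**What to change.** Before outcome data are seen:

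1. Declare one primary variable. The natural choice is the average 24-hour concentration of dihydrocaffeic acid-3'-sulfate, since the trial was sized on it. One predefined total phenolic concentration would also do, but needs its own sizing.
2. Declare one primary contrast, three cups versus one cup, as a two-sided 5% test. Test the other two arm contrasts in a fixed order after it.
3. Report the remaining phenolic metabolites as supportive, with 95% confidence intervals and Benjamini-Hochberg control at 5%.
4. State the sidedness and which standard deviation 870 is, and restate the power: on the paired-difference reading, 19 completers are needed two-sided, not 15.

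The cost is wording and a little computation, with no new data. The other metabolites face a stricter threshold. The stated power also becomes less favourable: only 2 of the 21 can be lost before two-sided power falls below 80%. Presenting the cardiometabolic outcomes as exploratory, or with false discovery rate control, is optional.
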